##### Participation in the CDI-measures at T0 to T5

Parents/main caretakers will be informed by the PI when girls score > 12 on the CDI-2 (cut-off score for depression) by telephone and will be advised to contact their family doctor or the independent healthcare professional for advice.

##### Participation in the RCADS-measures at T0 to T5

Parents/main caretakers will be informed by the PI when girls will have a T-score > 65 on the RCDAS (cut-off score for anxiety disorder) by telephone and will be advised to contact their family doctor or the independent healthcare professional for advice.

##### Participation in the intervention condition (participating in the online training sessions and using the app)

Participating in the online training sessions

In this study, the potential for harm is defined as sustained deterioration in a girl’s functioning that is *attributable to the prevention program* [113]. To be able to manage (potential) harm caused by the online training sessions skillfully and in a protocolled manner, a risk management protocol has been developed by the PI and research team to provide a consistent approach to the identification, reporting, and follow-up of risks related to participation in the intervention condition. Following study procedures of Baer and colleagues [112], several questions will follow each training session and relating to unpleasant experiences during the sessions, perceived harm from the sessions, and support for any difficult experiences. Some will use Likert scales whereas others will request free-text responses. A written introduction to these questions noted that the practice of mindfulness can increase awareness of the full range of human experiences, including difficult thoughts, emotions, and sensations. Girls then will be asked how often they had such experiences during the course (with response options ranging from “*never*” to “*daily or almost daily*”) and how upsetting these experiences were (response options ranging from “*not at all*” to “*extremely*”). An open text response question will ask the girls to describe their unpleasant experiences during the mindfulness training in more detail. Next, harm will be defined for girls as being “worse off, in any way, after the course, then you would have been if you hadn’t done the course.” Girls will be asked how harmful the course is for them (response options ranging from “*not at all*” to “*extremely*”) and a free-response question will ask them to describe the harm in more detail. Finally, they will be asked if they had sought support for any difficult experiences and, if so, from whom and how helpful the support was. After each training sessions, trainers will send the questionnaires to the PI and she will contact girls who reported difficulties during the sessions within max. 3 days after the session, and she will provide appropriate support, eventually after consulting the independent health care professional.

It is also possible that there will be deteriorations in girls’ functioning as a result of *frictions with the dyad friend* during the intervention period. The training program consists of fourteen online meetings in which the dyads participate together. Each dyad has its own trainer who provides training during all meetings. Every meeting the trainers discuss with the dyads how the cooperation with the app and the homework assignments went in the previous practice period. These discussions have a signaling function: trainers will invite the girls to share all their experiences. We assume that girls will share any problems regarding, for example, their motivation and any frictions or disagreements with the trainers (or that these are observable by the trainers based on verbal and non-verbal behavior during the meetings), so that solutions can be found together. If necessary, trainers may also seek general advice with the teacher-mentors. These possible problems, solutions, and results are shared by the trainers during the intervisions, so that trainers can offer uniform advice as much as possible.

The use of the app is monitored at the individual level by the researchers. When girls do not fill in the diary and moodtracker for more than 3 days in a row, the researchers will pass this on to the trainers, because this may indicate motivation problems, whether this is caused by mutual friction or something else. But girls may also be sick, for example, which causes them to lose track of the app for a while. During the next meeting, the trainers will discuss the causes of non-response with the dyads and jointly look for solutions. Together with possible solutions and results, this information will also be shared by the trainers during the intervisions.

When girls talk about suicide, self-injury, sexual or physical abuse, substance abuse, or eating disorders during the online training sessions, the trainer will stop the session. In these cases, the coordinating researcher will immediately (by no contact within 24 h) contact the PI. The PI will contact the independent health care professional in case of severe problems. Depending on the situation, parents/main caretakers of both participants of the dyad or the school-mentor will be informed by the PI, depending on the specific topic. The PI will inform parents/main caretakers in situations of non-family-related acute problems and will advise them to contact the family doctor or the independent health care professional. In case of severe family-related problems, the PI will call inform the school-mentor. We will inform the mentor in case of family-related acute problems, so that the school will be able to decide to use the Veilig Thuis Protocol. In severe cases, the independent health care professional will also be consulted by the PI. In all situations, we protect the privacy of all participants. This implies that we only should inform parents/main caretakers or the mentor more in depth when the participant initiated the conversation about suicide, self-injury, sexual or physical abuse, or eating disorders. Girls will have to provide written informed consent for this part of the training separately before the PTT will start. The training sessions will be continued after this procedure.

All reported difficulties and support provided will be logged in the research team logbook. This part of the intervention protocol will be discussed and agreed with the headteachers/teacher-mentors of the participating dyads and will be explained in the participant information sheets for parents and girls.

Using the app

Because the App yourself Happy app will collect high-risk personal (health) data in order to monitor the program fidelity and to supervise the trainers (i.e., this process will be the responsibility of the PI), the Chief Privacy Officer of the Rotterdam University of Applied Sciences and the Data Steward conducted a Data Protection Impact Assessment (DPIA), which was finalized in December 2022. Rotterdam University of Applied Sciences and YipYip (i.e., the company who is leading on the technical development and design of the App yourself Happy app) have conducted a “Data Verwerkersovereenkomst.” In sum: all risks have been analyzed and this process resulted in several mitigating measures. The only identified residual risk with moderate risk status concerns the following: “Appropriate agreements have been made with YipYip and the VU about the processing of personal data recorded in a processing agreement. YipYip has an ISO/IEC27001:2017 and NEN 7510–1:2017 certification that are both valid until April 2025. YipYip uses the ‘subverwerker’ Google Cloud Platform. The company is in the United States, but data storage takes place in the Netherlands. YipYip has indicated to have appropriate agreements with Google and is Google ISO 27001 and NEN 7510 certified. Any residual risk at American cloud providers cannot be ruled out.”

## Data management

### Sharing during research

In order to facilitate co-operative research over long-distance and only if necessary, research data including personal data may be shared among the PI and all researchers (including the data manager). Data linked to published papers will be made openly available minus any data that can be considered personal data (e.g., video data). For the purpose of sharing pseudonymized research data over distance, researchers will use ResearchDrive or the Dutch cloud service SURFdrive. SURFdrive is designed specifically for higher education and research purposes and offers researchers and staff an easy and safe way to share and synchronize files within a secure community cloud with ample storage capacity. All SURFdrive information security protocols meet high standards. The Dutch Legal Framework for Cloud Services serves as a guideline for all service-related agreements. SURFdrive complies with Dutch and European privacy legislation. In addition, access to SURFdrive is password protected and designated folders can be password protected. Communication to and from SURFdrive is encrypted. If shared via SURFdrive, files that contain personal data are placed in designated and password-protected folders. In addition, such shared files will be encrypted. Keys to encrypted shared files are held by the PI and secondary researchers.

### Sharing after research

When the study is completed, the underlying research data may be shared with third parties for the purposes of reproduction, reuse, or assessment of scientific integrity. The sharing of research data connected to a publication is subjected to contractual obligations with the publisher. Data linked to published papers will be made openly available minus any data that can be considered personal data (e.g., video data). The sharing of research data and codebook with third parties will be carried out with the use of DataverseNL. Files that contain personal data will not be stored on DataverseNL unless they are anonymized and/or pseudonymized. Files that contain personal data will be stored in YODA, an online archive for storing sensitive information/data with a persistent identifier. Files stored in YODA will not be shared with third parties, unless the purpose of reproduction, reuse, or assessment of scientific integrity justifies otherwise. In that event such files may be released subject to identification of the requestor accompanied by a purpose statement and approval by the competent authority of the Vrije Universiteit Amsterdam.

### Dissemination policy

Research findings of the HFPM cRCT will be presented in open access high-quality peer review journals and via magazines for teacher- and health care professionals and through presentations at variety of academic conferences. Furthermore, the research findings will be presented to participants (i.e., girls, parents/main caretakers and schools) via management letters and the study website: www.happyfriends.app..

## Discussion

The proposed study aims to provide insight into the short-term (T1, T2, T3 and T4) and long-term effects (T5) of the HFPM secondary school-edition prevention program on girls’ co-rumination, internalizing problems, wellbeing, and social-emotional behavioral functioning.

The HFPM program is school-based mindfulness and psychoeducation blended prevention program aimed at girls aged 13–15 years within secondary schools. This program was developed between 2020 and 2023 using the Intervention Mapping Approach for planning health promotion programs. The program comprises of 14 guided, weekly online lessons with mindfulness practices and psychoeducation, guiding the dyadic use of the application App yourself Happy. The goal of this program is to train 160 Dutch (80 dyads) high-risk girls between ages 13 and 15 to shift dyadic maladaptive ER patterns to more adaptive ER strategies within their dyadic interactions, while continuing to reap the benefits of their close, intimate friendships and exploring healthy, new alternatives for excessive co-rumination.

The objective of the HFPM cRCT is to evaluate the effectiveness of the prevention program HFPM, delivered by experienced mindfulness health professionals, compared with CAU and to unveil mechanisms of change. Self-reported risk for (early onset) depression and anxiety and self-reported and observed co-rumination will be the primary outcomes. Secondary outcomes will be self- and friend-reported friendship quality, self-reported positive and negative affect, self-reported interpersonal reactivity to personal distress, self-reported interpersonal responses to positive affect, self-reported anhedonic symptoms, self-reported mastery, and parent-reported health care use.

If the trial demonstrates that this prevention program is effective, secondary schools will be able to prevent excessive co-rumination in young adolescent girls and to improve girls’ short- and long-term mental health outcomes and friendship quality. The trial will also contribute to our understanding for whom, and under which circumstances, the prevention program is most effective, so schools will be able to match the intervention working mechanisms with the specific needs of subgroups of girls within schools. This knowledge will result in continuous improvements in the development of the train-the-trainer program, including training and supervision of HFPM trainers in order to maximize implementation quality and fidelity.

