The objective of the HFPM cluster Randomized Controlled Trial (cRCT) is to evaluate the effectiveness of the prevention program HFPM, delivered by experienced mindfulness health professionals, compared with care-as-usual (CAU) and to unveil mechanisms of change. Given that, to date, no other interventions are available that target excessive co-rumination between adolescent girls, girls in the control condition will receive CUA to test whether our prevention program has additional value above what is usually done in their routine care. The main research questions are:What is the effectiveness of the Happy Friends, Positive Minds mindfulness-based prevention program on levels of co-rumination and risk for early-onset depression and anxiety in Dutch adolescent girls from age 13 to 15 years old?What is the effectiveness of the Happy Friends, Positive Minds mindfulness-based prevention program on friendship quality, levels of self-reported positive and negative affect, interpersonal reactivity to personal distress, interpersonal responses to positive affect, anhedonic symptoms, mastery, and health care use in Dutch adolescent girls from age 13 to 15 years old?

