### Sample size calculation

Multi-level models are used with individuals nested in dyads. With a clinical relevant effect size, that is, a difference of 1 *SD* (i.e., Cohen’s *d* = 1) between the control and intervention group where high-risk girls (*M* + 1 *SD*) score on average similar to non-high-risk girls on co-rumination (*M*) after the intervention, and a small to moderate effect association between co-rumination and internalizing problems (Cohen’s *d* = 0.50; [15]), which will result in a possible reduction of depressive feelings with 0.50 *SD*, and an ICC of depressive feelings within dyads of 0.20, 80 dyads (40 control, 40 intervention) will be required (Optimal Design; [62]). However, we will aim to oversample to a maximum of 160 dyads in order to identify smaller effects (Cohen’s *d* = 0.35) that are potentially relevant for theory development, as well as our hypothesized mediating and moderating factors as described in the “Data analysis plan” section.

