### Secondary outcome variables

#### T0, T1, T2, T3, T4, and 1-year follow-up measures T5 (girls)

##### Self-reported (early-onset risk for) generalized anxiety symptoms/disorder

Self-reported generalized anxiety disorder will be measured with the Dutch version of the subscale generalized anxiety disorder (GAD) of the Revised Children’s Anxiety and Depression Scale (RCADS; [70]). This scale has six items (e.g., “I worry about things”) and assesses generalized anxiety on a 4-point scale (0 = *never*, 3 = *always*). The RCADS has good psychometric properties and has demonstrated excellent reliability and validity [70, 71]. We will use the official Dutch translation of the RCADS, which is freely available. The Dutch version of the RCADS—subscale GAD—showed good internal consistency, validity, and sensitivity to change [72].

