##### Self-reported problem anxiety talk

Self-reported problem anxiety talk will be measured with the Dutch version of the Problem Anxiety Talk Scale (PATS; [73]). The items are developed to reflect (1) repetitive focus on anxiety‐related topics; (2) threatening interpretations of ambiguous situations; (3) anticipating the likelihood of future negative stressful events; and (4) lack of confidence about successfully coping with stressors. Instructions prompt girls to report on specific verbal interchanges during conversations with their same‐gender best friend with the phrase “When we talk about our worries…” Girls will rate the extent that each item reflects their conversations on a 5‐point Likert scale ranging from 1 (*not at all true*) to 5 (*very true*). Examples of items include “Once I start discussing my worries with my friend, we find it hard to stop,” (i.e., repetitive focus on anxiety‐provoking topics), “My friend often helps me think of possible risks or bad things that might happen,” (i.e., threatening appraisal), “When we discuss bad things that could happen, we talk as if the bad thing will definitely happen” (i.e., likelihood of negative events), and “When my friend and I discuss my worries I start to question my ability to handle future problems. (i.e., lack of confidence in coping skills). The PATS is scored as the sum of all scale items, ranging from 12 to 60 [73]. The PATS demonstrates strong internal consistency (Cronbach’s *α* = 0.89).

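### Anxiety is a primary outcome in the Discussion but a secondary one in Methods; separately, the CDI-2 parent-notification rule misses a score of exactly 12

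*Protocol article*

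**What the plan says.** **Rank of anxiety.** The Discussion of the protocol article states: "Self-reported risk for (early onset) depression and anxiety and self-reported and observed co-rumination will be the primary outcomes". The next sentence begins "Secondary outcomes will be self- and friend-reported friendship quality, self-reported positive and negative affect, self-reported interpersonal reactivity to personal distress" and goes on to responses to positive affect, anhedonia, mastery and health care use. Anxiety is not on that secondary list.

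Methods is organised under two explicit headings. *Primary outcome variables* holds self-reported co-rumination (CRQ-short), depressive symptoms (CDI-2) and observed co-rumination (Problem Talk Task). *Secondary outcome variables* opens with "Self-reported (early-onset risk for) generalized anxiety symptoms/disorder", measured by the RCADS generalized anxiety subscale.

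Three other places touch on the matter:

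- Research question 1, at the end of the Background, asks about "levels of co-rumination and risk for early-onset depression and anxiety in Dutch adolescent girls". Question 2 covers "friendship quality, levels of self-reported positive and negative affect, interpersonal reactivity to personal distress, interpersonal responses to positive affect, anhedonic symptoms, mastery"; the last item on its list is the use of health services.
- *Sample size calculation* carries its effect through to a 0.50 SD reduction in depressive feelings and uses "an ICC of depressive feelings within dyads of 0.20, 80 dyads (40 control, 40 intervention) will be required".
- The abstract gives a single list of outcomes without ranks.

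**CDI-2 threshold.** The description of the CDI-2 under *Primary outcome variables* gives a range of 0 to 56 and treats 12 and upward as clinically relevant. The section on participation in the CDI measures at T0 to T5 has parents telephoned when the score is strictly greater than 12, and calls that the cut-off for depression.

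**The concern.** Ranking outcomes in advance prevents the emphasis from being chosen once the results are known. Here the published text supports both choices. Under hypothesis 3 the trial will test the onset of anxiety symptoms and disorder. A favourable result could be presented as primary by pointing to the Discussion, and an unfavourable one as secondary by pointing to Methods. Girls, parents, schools and research staff all know the allocation, and the anxiety scale is self-reported, so the ranking is one of the few safeguards on how much weight the result carries.

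The CDI-2 mismatch has a different consequence. A girl who scores exactly 12 is in the clinically relevant range by one section, yet the notification rule in the other does not have her parents called.

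**Working it through.** **1. The two sets of primary outcomes, side by side**

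| Outcome | Methods | Discussion |
|---|---|---|
| Self-reported co-rumination | primary | primary |
| Observed co-rumination | primary | primary |
| Depression (CDI-2) | primary | primary |
| Anxiety (RCADS generalized anxiety) | secondary | primary |
| Number of primary outcomes | 3 | 4 |

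The difference is 4 − 3 = 1, and that one is anxiety. If co-rumination is counted once rather than by its two measures, the split is 2 against 3 and the conflict is the same. It is also the same outcome in both places: the Discussion and the Methods subheading both speak of early-onset risk, and RCADS is the only scale of anxiety symptoms described.

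**2. Does any other section decide it?**

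- *Research questions.* Question 1 groups anxiety with the primary outcomes, and question 2 lists the same seven outcomes in the same order as the Discussion's secondary list. But both are introduced as main questions and neither is given a rank.
- *Abstract.* No ranks.
- *Data analysis plan.* Organised by hypothesis, without ranks.
- *Sample size.* Inputs: effect 0.50 SD on depressive feelings, ICC 0.20, m = 2 girls per dyad, J = 80 dyads. The section states neither significance level nor power; I assume two-sided 0.05 and aim for 80%.

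Variance of the arm difference in SD units = 4 × (ICC + (1 − ICC)/m)/J = 4 × (0.20 + 0.80/2)/80 = 4 × 0.60/80 = 0.030.

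Standard error = √0.030 = 0.173. Noncentrality = 0.50/0.173 = 2.89 on 78 degrees of freedom. Power = 81.4%.

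The smallest number of dyads reaching 80% is 78, close to the stated 80. For the larger target of 160 dyads and an effect of 0.35, the variance is 4 × 0.60/160 = 0.015 and power is 81.1%. Under these assumptions the calculation is fully accounted for by depressive feelings; anxiety plays no part in it. That leans towards the Methods ranking, but the section does not say which outcomes are primary, so it does not decide the matter.

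**3. What changes with the rank?** None of the models set out for the hypotheses depends on whether anxiety is primary or secondary. What changes is how its result is labelled and weighed.

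**4. CDI-2.** Whole-number scores from 0 to 56 give 57 possible values. The rules of 12 and upward and of strictly above 12 agree on 56 of them and differ on 1, the score 12. The article gives no distribution of scores, so the number of girls affected is unknown.

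**The case against.** The strongest reply is that Methods is the operative section. It has explicit headings, a later section refers back to it for the Problem Talk Task, and the sample size fits it. On this view the Discussion sentence is a loose summary, the registry entry and supplementary SAP may already fix the rank, and the matter is one of reporting rather than analysis. Much of this stands. It is a good reason to make the Methods ranking the default, and to treat the point as a correction rather than a flaw in design. It does not remove the conflict: the article states a rank twice, in incompatible ways, so one statement is wrong whatever the SAP says.

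Three stronger readings are tempting, and the documents do not support them.

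- *That research question 1 makes anxiety primary.* Grouping does not fix rank in this article. Hypothesis 1 groups negative affect with co-rumination, yet negative affect is secondary in both lists.
- *That the sample size is neutral, or covers anxiety.* A reader might infer this from "a small to moderate effect association between co-rumination and internalizing problems". The same sentence goes on to turn that association into a reduction in depressive feelings, and the ICC is for depressive feelings too.
- *That a fourth primary outcome raises the error rate by a known amount.* With independent tests at 0.05 and no adjustment, the chance of at least one false positive would be 1 − 0.95³ = 14.3% for three and 1 − 0.95⁴ = 18.5% for four. The article states neither a level per test nor a multiplicity rule, the outcomes are unlikely to be independent, and such rules may properly sit in the SAP. These figures illustrate the idea and do not describe this trial.

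On CDI-2, it can be said that the source of the cut-off is not visible and that the neighbouring RCADS notification rule also uses a strict inequality. Both are true. The direction of the correction therefore rests on the article's own statement of what is clinically relevant, and on the caution that suits a notification rule for minors. A reader might also infer that the depression-onset analysis is affected. The article does not say how onset is coded, so that does not follow.

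**Conclusion.** The contradiction is real and narrow. One outcome, anxiety, is primary in the Discussion and secondary in Methods. The weight of the article's other content leans towards Methods without settling it. The consequence is limited to the status an anxiety result may claim; sample size, measures, visits and stated models are untouched. Whether the registry or SAP resolves the rank cannot be judged from the article. It should be corrected, but it does not threaten the validity of the trial.

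The CDI-2 mismatch is a separate and smaller matter. It is confined to a single score and to the telephone notification of parents.

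**What to change.** Before outcome data are analysed, the sponsor should give anxiety one rank, the one in the registry and SAP, and state it identically wherever ranks appear.

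- **Default, unless those sources say otherwise:** keep the Methods classification, remove anxiety from the primary sentence in the Discussion, and name the RCADS generalized anxiety subscale in the secondary sentence there. Research question 1 need not change, since it assigns no rank.
- **If the registry and SAP make anxiety primary:** move the RCADS subsection under *Primary outcome variables* instead.

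Separately, change the CDI-2 notification rule from strictly above 12 to 12 or higher, so that it agrees with the description of the measure.

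The cost is two edited sentences (or one moved subsection) and one changed symbol. The only practical downside is a few more telephone calls to parents.
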